**Primary endpoints**

1. *Feasibility of recruitment and retention to the trial*: Data will comprise counts/ proportion of those who express interest, are screened and deemed eligible, those who consent, attrition and reasons for attrition if known
2. *Acceptability of the intervention to participants*: Adherence data will be collected (i.e. number/proportion of treatment sessions attended; reasons for non-attendance). Interview data will illuminate participants’ views about the intervention together with scores on the Session Rating Scale (4 items completed within the qualitative interview)
3. *Acceptability of research procedures and outcome measures*: Data will comprise attrition rates and rates of missing data; and qualitative participant interview data on the study experience and procedures

**Secondary endpoints**

1. *Appropriateness of outcome measures*: includes level of variability of scores; missing data; floor and ceiling effects; whether scale constructs align with concepts described by participants during in-depth interviews; and participant in-depth interview on acceptability of measures
2. *Estimating sample size*: based on means and standard deviations and effect sizes of the proposed primary clinical outcome measures (linguistic outcomes, see below) and retention rates.
3. *Assessing treatment fidelity processes*: includes acceptability of fidelity checking processes to participants; utility and reliability of fidelity checklist; extent to which treatment is delivered as intended (as prescribed in the therapy manual)

***Outcome Measures***

All proposed assessments have good psychometric properties. Most were developed for people with aphasia and all have been used in previous aphasia therapy studies. They have also been recently reviewed and discussed by our advisory group of people with aphasia and speech therapists (meeting 05/11/2019). Currently the assessments in total take 2 hours and 20 minutes. In combination with telling the two narratives (15 mins each) and the demographic questions (<10 mins) there is ample time within the proposed 4 hours at each time point to allow for breaks. Order of assessments will be randomly determined. The proposed clinical assessments are:

1. Personal narratives measure (LUNA Discourse Protocol): proposed as possible primary outcome measure in a future trial. Participants will produce two personal narratives at each assessment point, which will be video/audio recorded. They will be given standard scripted instructions specifying the possible topics, the length and how the story should be delivered. The narrative will be spoken to the assessing therapist. S/he will not provide any cues or ask questions. S/he may request further output (‘Can you tell me more’) or check whether the story is complete (‘Have you told me everything?’). Recording will cease when the participant indicates that the story is finished. Discourse samples will be analysed according to the LUNA Research Discourse Analysis Protocol. The analysis will be conducted by non-treating therapists/researchers who are blinded to group allocation. The analysis yields the following data: number and %narrative words, and number of narrative words/minute; %CIUs; number of CIUs/minute; %complete utterances; %single versus multi-clause utterances; #1, 2, and 3 argument utterances; Predicate Argument Score; story grammar count of elements; global coherence score; local coherence score; reference chains count; and overall listener judgment. Number of narrative words is proposed as the primary discourse outcome.
2. The Western Aphasia Battery-Revised Aphasia Quotient (WAB-R AQ). This measure tests speaking, auditory comprehension, naming and repetition across 4 sections and takes 30-45 minutes to administer. It is internationally used and has been recommended as a core outcome measure for aphasia trials (Wallace et al, 2019). It provides information on type of aphasia, and severity and has been tested for remote delivery (Dekhtyar et al, 2020).
3. The Communicative Participation Item Bank (CPIB) – General Short Form [PROM]. This comprises 10 items which are rated according to the level of interference caused by the person’s condition. For example, one asks about the interference with communicating when out in the community. The measure was designed for adults with communication disorders with substantial input from individuals themselves. The short form has proven appropriate for people with aphasia (Baylor et al., 2017). We anticipate overlap in item content of the CPIB with the ALA, however, we are intentionally including this instrument as it is possible that this much shorter instrument may be more acceptable (for its brevity) and on post-hoc analysis from the interviews, may align more with participants’ perceptions of benefit from the intervention. This will contribute to decision-making for a future large trial. <15 minutes.
4. The Communication Confidence Rating Scale for Aphasia (CCRSA) [PROM]; 10 items. This is the only confidence measure in our field and is increasingly used in treatment studies. It takes <10minutes.
5. The Assessment for Living with Aphasia (ALA) [PROM]. This is a 45 item pictographic self-report test of aphasia-related quality of life, created by an internationally leading charity in Canada. It is increasingly used in treatment studies and takes up to 45 minutes.

We are removing the Warwick Edinburgh Mental Wellbeing Scale (WEMWBS) [PROM]; 14 items. We believe that the item content within will be too influenced by COVID-19 circumstances and thus will not yield useful data and will also add an unnecessary burden on participants.

***Primary and secondary outcomes***

The primary clinical outcome is discourse as measured through the LUNA Discourse Protocol. Secondary clinical outcomes include language (WAB-R AQ only); communicative participation (CPIB); communicative confidence (CCRSA); and aphasia-related quality of life (ALA).

***Profiling assessments***

*Profiling and co-variate measures:* the FAST is completed during screening; the WAB-R-AQ is used at baseline; and the Raven’s Coloured Progressive Matrices (RCPM) is used at baseline.

We have removed the Corsi block tapping assessment (Kessels et al., 2000). It is a nonverbal measure of executive working memory, however this cannot be completed remotely. We have replaced this with the RCPM which is a world-recognised non-verbal assessment of cognition. It will illustrate participants’ abilities to manage the multi-level integrated nature of the therapy used as well as the meta-linguistic and cognitive approach adopted in the intervention. It consists of 3 sets of 12 items each where the participant must match a smaller stimulus figure into a larger whole (all visual). The RCPM is embedded in the WAB-R.

**Sample size**

This is a feasibility study, so is not powered to provide definitive data about the benefits of the intervention. Our sample size is based on recommended guidance for pilot or feasibility studies i.e. 12 per group (Julious, 2005) and is also the maximum number we can achieve in the time and resources available. We are seeking to recruit 24 participants. Allowing for some attrition this will hopefully ensure that 20 complete the study.

**Data management and monitoring**

A de-identified master dataset will be created and used for all main analyses. This will be stored on a password protected server accessible only to the research team. We note that de-identified data constitutes personal data. Personal data will be stored in electronic form for 10 years after the study has ended. The dataset will be monitored and updated by the PIs at least monthly.

Audio/digital recording interviewees or video recording will be saved onto encrypted devices and only transferred via encrypted files. Direct quotes will always be de-identified using participant number but also mindful of content which might unwittingly identify participants to their regular care group.

Paper records will not be generated until after lockdown has ceased and are anticipated to be minimal. All paper-based data will be kept in a locked filing cabinet at City, University of London. Data and identifiers will be kept in separate, locked filing cabinets. All data will be stored within a secure swipe-card protected area. Paper data will be converted to electronic form as appropriate, and paper documentation shredded and disposed of in confidential waste sacks as soon as possible.

All digital files will be deidentified as far as possible (i.e. video files will not have names attached) and will be stored on password protected computer files and stored securely in OneDrive. Zoom recordings will be saved on the local device, not in cloud storage. Storage on encrypted devices (e.g. laptop, hard drive, USB) will be used for any local data transfer. To enable data sharing with the two international grant co-applicants ([name] and [name]) will we establish a data sharing agreement and ensure that legal safeguards are in place (e.g. standard contractual clauses). This will be led by PI [name] with [name] (Information Assurance Team Leader, IT, City).

We will keep deidentified electronic data for the requisite 10 years as required by City, University of London. For linked student projects, data will be kept beyond the recommended time period (their graduation), as data is likely to contribute to an ongoing transcription reliability project, with future student research projects assessing reliability of other remaining personal narratives. We will ensure secure destruction of any electronic data uses the university's Information Services, with requests logged through IT Service Now.

**Analyses**

***Quantitative analysis***

The main quantitative analyses will be descriptive ones (n%) to ascertain feasibility parameters such as recruitment and attrition. However preliminary power calculations will be conducted bases on effect sizes (Cohens’ d and partial eta squared) to determine sample size for future full clinical trial of LUNA compared to usual care. In addition, correlational analysis will help to identify which factors associate optimum response to LUNA intervention.

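### The future trial is to be sized partly from the Cohen's d and partial eta squared observed in 20 to 24 people, which are too imprecise for that use

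*Protocol*

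**What the plan says.** Under Quantitative analysis, the Protocol makes the main analyses descriptive and then adds that "preliminary power calculations will be conducted bases on effect sizes". The effect sizes are Cohen's d and "partial eta squared) to determine sample size for future full clinical trial of LUNA compared to usual care".

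Secondary endpoints, item 2, makes sample size estimation an endpoint, "based on means and standard deviations and effect sizes of the proposed primary clinical outcome measures (linguistic outcomes, see below) and retention rates".

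The Sample size section says: "Our sample size is based on recommended guidance for pilot or feasibility studies i.e. 12 per group". It continues: "We are seeking to recruit 24 participants". It then adds: "Allowing for some attrition this will hopefully ensure that 20 complete the study". The same section says the study "is not powered to provide definitive data about the benefits of the intervention".

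The Protocol names no target difference for the future trial. It attaches no interval or bias correction to the effect sizes used for planning.

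**The concern.** A power calculation needs two kinds of input. One is the difference the trial should be able to detect, which is a judgement about what is worthwhile. The other is the set of nuisance quantities: variability, correlation with baseline and dropout. A small study can inform the second kind. Its observed effect is a poor substitute for the first, because required size varies with 1/d², so sampling error in d is greatly magnified.

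The Protocol accepts that the study cannot settle benefit, yet makes the estimate of benefit one of the inputs to the next trial's size. A chance high result would then support a full trial that is too small to detect the real effect. Partial eta squared adds a second problem: it cannot be negative, so on average it shows some effect even when there is none.

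**Working it through.** **Inputs from the Protocol.** 12 per group, 24 recruited, about 20 completing (Sample size); Cohen's d and partial eta squared as planning effects (Quantitative analysis). The stated size reproduces: 2 × 12 = 24, and 20 / (1 − 4/24) = 24, an implied attrition of 16.7%. It is a rule of thumb and is not in dispute.

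**Assumptions, because the Protocol gives no figures.** Future trial: two equal arms, two-sided 5%, 80% power. True d: 0.3, 0.5 and 0.8. Pilot: 10 or 12 per group, no baseline adjustment.

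**1. Interval around an observed d.** Inverting the noncentral t, an observed d of 0.5 has a 95% CI of −0.40 to 1.38 with 10 per group and −0.32 to 1.31 with 12. Required n per arm is 2 × (1.960 + 0.842)² / d² = 15.70 / d². The point estimate gives 15.70 / 0.25 = 62.8, so 63 per arm. The upper limit gives 9 to 10 per arm, and the lower limit gives no finite size. Even an observed d of 0.8 has an interval that includes zero: −0.12 to 1.70 (10 per group), −0.04 to 1.63 (12 per group).

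**2. When the full trial is badly underpowered.** A trial sized at the observed d has real power Φ(2.802 × true d / observed d − 1.960). This is below 50% when the observed d exceeds 2.802 / 1.960 = 1.43 times the true d. The chance of that follows from the noncentral t and was confirmed by simulation with sizes rounded up:

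| True d | Under 50% power, 12 per group | Under 50% power, 10 per group |
|---|---|---|
| 0.3 | 38% | 39% |
| 0.5 | 31% | 32% |
| 0.8 | 23% | 25% |

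Pilots with d at or below zero do not enter these figures. They yield no usable size, and at a true d of 0.5 they make up 11% (12 per group) to 13% (10 per group) of pilots.

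**3. Spread of planned sizes.** At a true d of 0.5 the right size is 63 per arm. The middle half of planned sizes runs from about 25 to about 310 per arm with 12 per group, and from about 23 to about 390 with 10. Only 9-10% of pilots land within 20% of 63.

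**4. Partial eta squared.** For a two-group contrast it equals t² / (t² + df). Under no effect its mean is 1 / (1 + df): 1/23 = 0.043 for N = 24 and 1/19 = 0.053 for N = 20. Its median is 0.021 and 0.026. Converting by d = 2√(η² / (1 − η²)), the means correspond to d of 0.43 and 0.47 (87 and 71 per arm). The medians correspond to 0.29 and 0.32 (about 184 and 149 per arm). All of these are finite sizes for a treatment that does nothing. At a true d of 0.5 the true value is 0.25 / 4.25 = 0.059, while the mean estimate is 0.098 (N = 24) to 0.106 (N = 20). Cohen's d itself is biased upward by only 3-5%.

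**5. Baseline adjustment.** With 12 per group the half-width for the difference, in SD units, falls from 0.85 to 0.61 at an assumed T1-T2 correlation of 0.7, and to 0.37 at 0.9. Even at 0.9, an observed 0.5 runs from 0.13 to 0.87, and the sizes at the two ends differ by a factor of (0.87 / 0.13)² ≈ 45.

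**6. The alternative.** With the target difference fixed in advance, only the SD is uncertain. Its 95% CI is 0.77 to 1.42 times the estimate on 22 df and 0.76 to 1.48 times on 18 df. Size varies with the square of the SD, so the required size lies between 0.60 and 2.00 times (22 df) or 0.57 and 2.19 times (18 df) the planned one. That range is wide, but it is bounded.

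**The case against.** The best defence is that the planned basis is broader than effect sizes alone. Secondary endpoints, item 2, also lists means, SDs and retention, and Quantitative analysis calls the calculations preliminary. That stands: a reader might infer that observed effects are the only input, and the text does not support this. Effect sizes nevertheless remain a stated basis, the stated purpose is to determine the size, and no other target difference is named.

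The error rates depend on the unknown true effect and are milder when it is large. Adjusting for T1 would also narrow the intervals. Both points are fair. They reduce the problem without removing it, and they mean the resulting size should not be called arbitrary.

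For a two-group contrast, partial eta squared carries the same information as d, and d keeps the sign. That too is fair: partial eta squared adds nothing to planning beyond d except the upward bias.

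Two stronger readings should be set aside. A reader might infer that the effect size will come from a group-by-time analysis over T1 to T3, so mixing in a time when both groups have been treated. The Protocol names no such model, and its Aims describe comparing people who have and have not received LUNA, which fits T2. A reader might also infer that a small observed effect would end the programme. Nothing makes d a progression criterion; the primary endpoints concern recruitment, retention, adherence and acceptability.

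**Conclusion.** The concern holds in this form: the effect observed in 20 to 24 people is too imprecise to serve as a planning effect, and partial eta squared is in addition biased upward and unsigned. The chance of an underpowered full trial is roughly one in four to two in five across true effects of 0.8 down to 0.3. This rests on an assumed two-sided 5% level, 80% power, no baseline adjustment, and mechanical use of the observed d.

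The statement that the study is not powered for benefit does not contradict the plan, but it is a reason against using the benefit estimate in this way. The 12 per group is not at fault. Nothing changes for this study's participants, conduct or primary endpoints, and the same data will support a sounder calculation. The point should be fixed, but it does not threaten the present study.

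**What to change.** Amend Secondary endpoints, item 2, and Quantitative analysis to say:

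- The future sample size will use this study's SD of the proposed primary outcome with allowance for its uncertainty, the T1-T2 correlation, and the retention rate with its interval.
- The target difference will be set separately as the smallest worthwhile change, informed by the advisory group and the participant interviews.
- The between-group d at T2 will be reported with its 95% CI as description only. Neither observed d nor partial eta squared will be used as the planning effect.

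An upper confidence limit is one reasonable way to allow for uncertainty in the SD. The one-sided 80% limit, for example, multiplies the SD by 1.16 on 22 df or 1.18 on 18 df. The level is a matter of choice.

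The cost is wording, plus some advisory group time to agree the difference. All the data are already to be collected. The downside is that the projected trial may look larger: the example limit alone raises it by about 35-40% (1.16² ≈ 1.35, 1.18² ≈ 1.39). The Protocol states that no data collection has begun, so the change can be made before any results are known.

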***Qualitative analysis***

We will follow the recommended Standards for Reporting Qualitative Research (<https://www.equator-network.org/reporting-guidelines/srqr/>). The primary source of data is in-depth individual interviews with participants. All interviews will be recorded with consent and transcribed verbatim. We will use Framework Analysis which means raw data is tagged or coded according to a thematic index, and then data is synthesized and can be considered according to theme and case.

**Patient and Public Involvement**

LUNA has patient and public involvement embedded at its core. Four speech and language therapists and four people with post-stroke aphasia have collaborated with the research team from the outset of the grant application process. They comprise the LUNA Advisory Group meeting periodically throughout the research project and were intensively involved as co-designers in Phase 3 determining the discourse assessment and outcome measures, and the treatment. They have also contributed on treatment fidelity criteria, the model of service delivery (qualified and supported with assistant), phase 4 therapist training, and manuals. They have advised on the remote data collection methods and are working regularly with the PIs and some research staff to practise online procedures. In future meetings they will advise on issues that arise in the trial, be involved in discussion and interpretation of the findings and their dissemination, and consider ways in which to harness the emerging community of practice that is developing from this project.

**Adverse events and post-trial care**

LUNA is exploring a non-invasive, low risk intervention so adverse events arising from participation are unlikely. All members of the LUNA team (Project Manager, RAs) will report adverse events to the project PIs, regardless of whether or not these events are connected to the activities of the project. Events will be recorded on a password protected computer drive. PIs will discuss how the adverse event is being managed with the reporting staff member. For example, this might include hospitalisation or contact with Social Services. If necessary additional steps will be taken, e.g. involving referrals to relevant services.  The team may also discuss whether continued involvement in the project is in the participant’s best interest.

Participating in this study is unlikely to cause harm or discomfort to participants. We have trialled LUNA on several individuals as case studies over the past 4 years and worked extensively with 4 people with aphasia for 6 months to codesign our current LUNA programme. Telling personal stories is not considered intrusive and is indeed welcomed by our PWA team who strongly advocate working on people’s own words and language in therapy. Participants will be discouraged (if necessary) from telling their “stroke story”; although important to individuals, it is not the focus of LUNA.

The intervention is not expected to cause distress however, procedures are in place in case this occurs. Some concerns may also arise from the social isolation experienced by individuals during COVID-19 lockdown. If distress is evident the individual leading the session with the participant will pause and discuss, and either take a break or discontinue the session as appropriate. S/he will discuss the cause of the distress and will support the participant in the session. S/he will raise the situation as soon as possible with a member of the City-based research team, and jointly consider appropriate course(s) of action. S/he will discuss and agree a course of action then with the participant and implement and monitor this. This may include encouraging the participant to make contact with their GP for support, and/or contacting The Stroke Association for support (depending on the nature of the concern). Therapy assistants are not expected to be sufficiently skilled to lead this and are supervised, therefore the staff member will manage this on their behalf.

**Dissemination policy**

At the end of the study, each participant will be provided with a feedback sheet detailing his/her individual results on the outcome measures. At the end of the study, all participants will be also provided with a summary of the main findings. This will be paper-based/ written in Microsoft Word and supported with graphics and images. It will be written in a style considered accessible for people with mild to moderate aphasia. This brief brochure will be posted or emailed to participants (their preference). It will also be available publicly on the project website <https://blogs.city.ac.uk/luna>. If social isolation measures stop in time, all participants will be invited to a dissemination day at City, which will report on our main findings of the study. Our team has run several events of this kind, linked to each of our past research projects. Finally, we will write academic peer-reviewed journal articles and submit abstracts to academic conferences.

